**Attitudes outcomes:**				
		Student acceptance of teacher violence	3 items will be constructed as a continuous outcome. Each response option will be assigned a score of 0–3. Scores summed and modeled as continuous score range 0 (low) to 9 (high acceptability)	Measure from the Good Schools Study [41]
		Adolescents attitudes toward gender relations	18 items will be initially explored as one construct to generate a continuous outcome. Response options numerally coded 0-3 and individual scores calculated, ranging from 0-54. Attitudes toward domestic violence from Gender Equitable Men subscale 5 items will be explored as a continuous outcome and as single question items.	Gender Equitable Men scale, Uganda version [54]
**Outcomes supportive of resilience:**				
		Agency	13 items, 3 independent dimensions, Internality (4 items), Powerful Others (4 items), and Chance (5 items). Each subscale will be initially explored as separate continuous outcome measures, response options will be assigned a score 0-3, summed and modeled as continuous scores.	Adapted Internality, Powerful Others, and Chance measure of locus of control, short-form
		Self-regulation	13 items will be initially explored as one construct (one continuous outcome), and further explored as a 2-dimensional measure, with restraint and impulsivity modeled as separate continuous outcomes [55,56].	Brief Self-Control Scale [57]
		Social assets	Continuous outcome, 8 items with response options: 0 not true, 1 somewhat true, and 2 certainly true. scores summed and modeled as continuous score range 0-16	Constructed from subsets of the Strengths and Difficulties Questionnaire [58,59]
		Psychological assets	Continuous outcome, 7 items, reverse coded: 2 not true, 1 somewhat true and 0 certainly true. Response options assigned a score 0-2, range: 0-14	Constructed from subsets of the Strengths and Difficulties Questionnaire [58,59]
		Peer connectedness	2 items, continuous outcome generated, response options numerally coded 0-3 and individual scores calculated, range 0-6.	Questions adapted from scales used in adolescent health behavior surveys [60] and used in Good Schools Study. Response options: all the time, most of the time, sometimes, or never
**Retention in school outcomes**				
		Staying in school	Last school grade completed will be assessed in relation to current age and grade at Wave 1, for example, binary outcomes: completion of grade Primary 7 (yes=1, no=0), transition to secondary school measured as completion of grade Secondary 1 (yes=1, no=0)	Not applicable

The primary outcome is peer violence victimization. A peer is defined as students, coworkers, or community members of a similar age. Adolescents’ self-reported experience of peer violence in the last year will be measured using an adapted subset of questions from the International Society for the Prevention of Child Abuse and Neglect Child Abuse Screening Tool—Child: Institutional [61]. Questions were previously piloted and used in the Wave 1 survey [32]. For this analysis, peer violence is defined as violence from students, coworkers, or community members of a similar age. Experience of past-year peer violence will be constructed as a composite binary measure, with positive responses to one or more question items on acts of physical, emotional, and sexual violence coded as 1, and no acts coded as 0.

Secondary violence outcomes will be constructed as single and composite binary measures—as described above—for the primary outcome. Secondary violence outcome measures include past-year self-reported use of peer violence, girls’ experience and boys’ use of intimate-partner violence, measured using question items from the WHO multicountry Study on Women’s Health and Domestic Violence [51] and Conflict in Adolescent Dating Relationships Inventory [52,53,62] adapted and used during Wave 1. Intimate partners include boy/girlfriends, husbands/wives, and casual dating partners. Self-reported intimate-partner violence will be explored as a combined measure and separately by violence type (emotional, physical, and sexual).

We will measure attitudes toward teacher violence with a 3-item measure developed for the Good Schools Study and used during the Wave 1 survey [41]. A shortened 18-item Gender Equitable Men scale, previously validated among Ugandan adolescents [54], will be used to measure gender-equitable attitudes. Question items and subsets of questions, including attitudes toward domestic violence, will be explored as single items and composite outcomes. Response options for all attitude questions are on a 4-point Likert-type scale.

Factors supportive of resilience will be measured, including peer connectedness [41], social assets, and psychological assets [63], these 3 measures had adequate internal consistency at Wave 1 [58,59,64]. The response options were on a 3-point scale for the asset questions and a 4-point Likert-type scale for the connectedness questions. Furthermore, we will explore using the Internality, Powerful Others, and Chance measure of locus of control, as a proxy measure of agency [65,66], and the Brief Self Control Scale [57,67], as a proxy to measure self-regulation. As neither Internality, Powerful Others, and Chance nor Brief Self Control Scale measures have been validated among Ugandan adolescents, questions were forward and backward translated by bilingual researchers, concepts were reviewed by a user group of Ugandan adolescents, wording was iteratively adapted through cognitive interviews with 8 to 15 adolescents, and the questions were pilot tested before inclusion in the Wave 2 survey questionnaire. If the outcomes measures for either have low internal consistency (Cronbach α<.65) then exploratory factor analysis will be considered to generate factors scores and groupings.

To measure retention in school, we will capture last school grade completed and assess this in relation to expected grade based on school grade at Wave 1 and current age.

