### Long-Term Effects: Conceptual Framework

A schematic that illustrates mechanisms through which the Good School Toolkit may achieve long-term effects is shown in Figure 2. The Good Schools Study’s quantitative and qualitative findings suggested that the toolkit intervention improved the schools’ operational culture and enhanced student capabilities, including improvements in student-teacher relationships; fostered attitudes that were less accepting of teacher violence; enhanced emotional support from peers; allowed enhanced school-connectedness; and improved self-regulation, voice, and motivation [28,31,39-41]. We hypothesize that students who experienced the toolkit intervention during their primary education (ie, were exposed to a supportive culture and less violence in a safer school environment) are less likely to drop out of school and therefore are retained in the education system for longer. Furthermore, we hypothesize that students’ enhanced capabilities—brought about by the toolkit intervention—can be retained through the transition out of primary school into new environments, equipping adolescents with individual skills supportive of resilience. Through these positive changes brought about by exposure to the toolkit intervention, we hypothesize that adolescents will have attitudes that are less accepting of violence, will be more gender-equitable, and will be less likely to perpetrate or experience peer and intimate partner violence in later adolescent relationships.

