### Good School Toolkit Exposure Measures

#### Primary

Participants in 21 trial intervention schools and those in the 21 wait-list control schools are categorized as the original study arms (1) trial and (2) wait-list control. Further subcategories defined within the wait-list control are adolescents who were attending Primary 5 or 6 in the 19 later delivery schools as the (2.1) later delivery exposure group; adolescents who attended one of the schools that did not implement the toolkit or who were attending Primary 7 in one of 19 later delivery schools at Wave 1 (as these students are expected to have left school prior to intervention delivery) as the (2.2) no exposure group (Figure 3).

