### Power to Detect a Difference

We anticipate that our trial exposure group will be 50% (n=1201), and no exposure group 19% (n=456), of the total Wave 2 sample (assuming a conservative 70% follow-up, 2402/3431). We estimate 50% [2] of our no exposure group will report past-year experiences of physical, emotional, or sexual violence from a peer at Wave 2. In this case, the smallest difference we can detect between no exposure and trial exposure groups, assuming 70% follow-up, an α of .5 and power of .8, would be an 8% difference between groups (OR 0.73).

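### Completion of Primary 7 compares unequal at-risk windows in trial vs no exposure, so the unadjusted contrast is biased against the toolkit and the grade-adjusted one is thin

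*Protocol article*

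**What the plan says.** The retention row of Table 2 (Study Outcome Measures) takes last grade completed, to be assessed against current age and Wave 1 grade. It offers two binary versions as examples: "completion of grade Primary 7 (yes=1, no=0), transition to secondary school measured as completion of grade Secondary 1 (yes=1, no=0". The text below the table repeats that attainment will be judged against the grade expected from Wave 1 grade and age.

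The exposure groups are defined under Good School Toolkit Exposure Measures, Primary. The no-exposure group (2.2) is "adolescents who attended one of the schools that did not implement the toolkit or who were attending Primary 7 in one of 19 later delivery", the last phrase referring to schools. The trial group (1) is everyone sampled in the 21 intervention schools, hence Primary 5 to 7. The sampling section says Primary 7 pupils were expected to have left primary school before delivery to wait-list schools began in 2015.

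The Regression Analysis Strategy lists 1 vs 2.2 first, then 1 vs 2, with a repeat that drops the two non-implementing schools. Unadjusted and adjusted models will both be presented for secondary outcomes, and potential confounders enter only the adjusted ones. School grade is a listed potential confounder or effect modifier, to be used as appropriate for the relationship in question.

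**The concern.** A pupil already in Primary 7 in 2014 can fail to complete it only by leaving in the remainder of that year, or by repeating and then leaving. A pupil in Primary 5 or 6 must first get through two or one further years. Apart from the two schools that declined, every no-exposure pupil was "attending Primary 7 in one of 19 later delivery schools at Wave 1". A plain yes/no for Primary 7 completion therefore favours the no-exposure group by construction.

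The conceptual framework hypothesizes that exposed pupils "are less likely to drop out of school and therefore are retained in the education system for longer". An unadjusted estimate pointing the other way would look like harm to schooling. A null after adjustment could be read as no lasting effect. The Discussion says that an absence of long-term impact on retention and the other outcomes would suggest further efforts are required, so either misreading could feed directly into the conclusions.

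**Working it through.** **The plan's own figure.** The only power statement concerns peer violence victimization: n=456 vs 1201, 50% in the reference group, power 0.8. A pooled normal approximation with two-sided alpha 0.05 gives a detectable difference of 7.66 points (OR 0.734), matching the stated 8% and OR 0.73. (Alpha is printed as .5, which does not reproduce them.) No figure is given for retention.

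**Grade mix of group 2.2.** Inputs from the power section: "We anticipate that our trial exposure group will be 50% (n=1201), and no exposure group 19% (n=456), of the total Wave 2 sample", total 2402. Assumption: the two declining schools are of average size.
- Pupils in those two schools: 2402 × 2/42 ≈ 114.
- Primary 7 pupils from the 19 later-delivery schools: 456 − 114 = 342.
- Primary 7 share in those 19 schools: 342/(1201 − 114) = 31.5%.
- Primary 7 pupils in the two schools: 0.315 × 114 ≈ 36.
- Primary 7 in group 2.2: (342 + 36)/456 ≈ 83%, leaving about 78 Primary 5 and 6 pupils.

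If the two schools together hold 182 to 60 pupils, the share is 71% to 91%, with 133 to 39 Primary 5 and 6 pupils.

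**Unadjusted odds ratio with no toolkit effect.** Assumptions, none in the document: completion q once in Primary 7, yearly dropout d before that, equal grade and school sizes. Completion by Wave 1 grade is q(1−d)² for Primary 5, q(1−d) for Primary 6 and q for Primary 7. Trial is the mean of the three. No exposure is (19/3 × q + 2 × mean)/(19/3 + 2).

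| q | d | Trial | No exposure | OR, 42 schools | OR, two schools dropped |
|---|---|---|---|---|---|
| 0.98 | 0.05 | 93.2% | 96.8% | 0.45 | 0.28 |
| 0.98 | 0.10 | 88.5% | 95.7% | 0.34 | 0.16 |
| 0.98 | 0.15 | 84.0% | 94.6% | 0.30 | 0.11 |
| 0.90 | 0.10 | 81.3% | 87.9% | 0.60 | 0.48 |
| 0.85 | 0.05 | 80.8% | 84.0% | 0.80 | 0.74 |

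A second model uses the same retention r in every grade and the 31.5% and 83% shares above. It gives 0.58 to 0.61 for r from 0.85 to 0.98. The size depends on the assumptions; the direction does not.

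**After conditioning on Wave 1 grade.** A grade-stratified Mantel-Haenszel simulation (2000 runs; trial 411, 411, 378 and no exposure 39, 39, 378 in Primary 5, 6, 7; no clustering) gives a null OR of about 1.00 and type I error of about 5%. Power for a halved yearly dropout is 99.7%, 95%, 74% and 41% at yearly retention 85%, 90%, 95% and 98%. For a dropout ratio of 0.73 it is 62%, 45%, 26% and 15%.

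Within Primary 7 alone (1201 × 0.315 ≈ 378 trial vs 378 unexposed), power for OR 1.37 (1/0.73) is:

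| Completion in Primary 7 | No clustering | Assumed design effect 2 |
|---|---|---|
| 80% | 38% | 21% |
| 90% | 23% | 14% |
| 95% | 14% | 9% |
| 98% | 8% | 6% |

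At 98% or above, even full completion in the trial group does not give 80% power. When the two schools are dropped, this stratum is all that informs the exposure effect.

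**Secondary 1 completion for comparison.** Taking 60% (the national transition figure in the Background) as the unexposed rate, the same Primary 7 stratum can detect about 9.7 points, or 13.5 with design effect 2.

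**The case against.** Much of the remedy is already in the text. Attainment is to be read against Wave 1 grade and expected grade, the binary forms are examples, Secondary 1 completion is named beside Primary 7 completion, and grade is a listed covariate. The plan also compares the original arms (1 vs 2), where both sides span Primary 5 to 7. Dropping the two schools is a repeat, not a replacement. All analyses are exploratory, and secondary outcomes are judged on size, direction and consistency.

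These points limit the consequence but do not remove the bias. No method is fixed for relating attainment to grade, the binary form as written ignores starting grade, and grade cannot enter the unadjusted model under the stated rule.

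A reader might go further and infer that Primary 7 completion cannot measure a toolkit effect in 1 vs 2.2 even after grade adjustment. The document does not support that. Trial Primary 7 and unexposed Primary 7 pupils have the same window, and the stratified analysis is unbiased under the null. A ceiling within Primary 7 is likewise only an assumption: the article gives no completion rate, no Wave 1 month and no grade counts.

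**Conclusion.** The point holds as a bias in the unadjusted 1 vs 2.2 contrast and as a loss of precision and scope in the adjusted one. It is not a failure of identification.

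With no toolkit effect, the unadjusted odds ratio is about 0.3 to 0.8 across Primary 7 completion of 85% to 98% and earlier yearly dropout of 5% to 15%, all assumed. The 83% Primary 7 share rests on average-sized schools. Grade adjustment removes the bias, but unexposed Primary 5 and 6 information then comes only from two schools that chose not to implement, and none remains when they are dropped. How weak the remaining Primary 7 comparison is depends on the unknown completion rate, and clustering would weaken it further.

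**What to change.** - For every retention outcome in 1 vs 2.2, include or stratify by Wave 1 grade in all models, including the one labelled unadjusted.
- Do not show Primary 7 completion for 1 vs 2.2 without grade stratification, and state that a null there will not be read as no effect on schooling.
- For this contrast, rely on Secondary 1 completion and on grade attained relative to grade expected, both within Wave 1 grade.
- Keep Primary 7 completion for 1 vs 2, noting that wait-list Primary 5 and 6 pupils in 19 schools were later offered the toolkit. Keep it also for 1 vs 2.1 restricted to Primary 5 and 6, labelled as earlier vs later delivery.

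This changes a few sentences and needs no new data, since Wave 1 grade and last grade completed are already captured. The price is lower precision and a narrower population, mainly Primary 7 pupils, for 1 vs 2.2.

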### Potential Confounders and Effect Modifiers

The following factors have been identified a priori as potential confounders or effect-modifiers to the exposure-outcome relationships of interest: biological sex and the number of meals eaten the previous day (as a proxy for socioeconomic status that is expected to be associated with staying in the study school throughout intervention delivery and associated with later violence outcomes). In addition, and as appropriate for specific exposure-outcome relationships, the following variables have been identified as potential effect-modifiers or confounders measured at Wave 1: school grade, family connectedness, and experiences of violence outside of school [68,69].

### Power to Detect a Difference

We anticipate that our trial exposure group will be 50% (n=1201), and no exposure group 19% (n=456), of the total Wave 2 sample (assuming a conservative 70% follow-up, 2402/3431). We estimate 50% [2] of our no exposure group will report past-year experiences of physical, emotional, or sexual violence from a peer at Wave 2. In this case, the smallest difference we can detect between no exposure and trial exposure groups, assuming 70% follow-up, an α of .5 and power of .8, would be an 8% difference between groups (OR 0.73).

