### Regression Analysis Strategy

All analysis is exploratory and hypotheses generating rather than testing. To explore if the intervention influences later outcomes, we will compare across the trial and no exposure groups (1 vs 2.2) and original study arms (1 vs 2) first including all 42 schools and then repeated, dropping the 2 nonimplementation schools. To further explore differences between levels of exposure, we plan to compare between trial and the later delivery groups (1 vs 2.1) and across secondary exposure groupings (Figure 3). We will account for clustering by including original study primary school as a random effect in mixed-effect regression models [71]. Binary outcomes will be analyzed using mixed-effect logistic regression, with effect size presented as odds ratios. Continuous outcomes will be analyzed using mixed-effects linear regression, with effect size presented as mean difference. All unadjusted and adjusted analyses will include baseline school-level mean of outcomes, where available [72]. Adjusted models will additionally include covariates identified as potential confounders. All measures of effect will be presented with 95% confidence intervals and *P* values. Size and direction of effect will be considered along with *P* values when assessing the strength of associations [70]. Appropriate methods will be used to analyze numeric outcomes that are not normally distributed. For example, bias-corrected 95% confidence intervals will be estimated using nonparametric bootstrapping. The presence of effect modification will be assessed by comparing models fitted with and without an interaction term. Likelihood ratio tests with *P* values<.1, along with the direction and size of effect for each group, will be considered as evidence for or against modification. If there is evidence of modification, then stratum-specific effects will be calculated [73].

For self-reported exposure, propensity score–matching will be used to account for the likelihood that self-reported exposure is confounded by an individual’s propensity to report exposure. We will estimate what factors predict toolkit exposure using regression analysis [29], then calculate predicted probability of exposure and group adolescents with similar propensity scores. The analysis will compare outcomes across these propensity score exposure groups, including the score as a covariate in regression models [72].

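### The stated detectable difference (8 points, OR 0.73) is a crude, unclustered two-proportion figure with alpha misprinted as .5, and it overstates the precision of the planned mixed models

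*Protocol article*

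**What the plan says.** Protocol article, Power to Detect a Difference: the trial group is put at 1201 (half the sample), against a "no exposure group 19% (n=456), of the total Wave 2 sample". That total is 2402 of the 3431 Wave 1 adolescents, a 70% follow-up that the article calls conservative. With 50% of the no exposure group reporting past-year peer violence, alpha printed as .5 and power of .8, it gives "the smallest difference we can detect between no exposure and trial exposure groups, assuming 70% follow-up" as 8 points, OR 0.73. No ICC, design effect or covariate is mentioned.

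Good School Toolkit Exposure Measures, Primary: group 1 (trial) holds all participants from 21 schools, sampled across Primary 5 to 7. Group 2.2 (no exposure) holds everyone from the 2 schools that did not implement, plus those "who were attending Primary 7 in one of 19 later delivery schools at Wave 1".

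Potential Confounders and Effect Modifiers: sex and number of meals are named a priori. Wave 1 grade is then listed, beside family connectedness and violence away from school, as a possible confounder or effect modifier, with the qualifier that these variables apply as appropriate to the relationship studied.

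Regression Analysis Strategy: original primary school enters the mixed models as a random effect, and "Adjusted models will additionally include covariates identified as potential confounders". The comparisons of 1 vs 2.2 and 1 vs 2 are planned "first including all 42 schools and then repeated, dropping the 2 nonimplementation schools". All analysis is declared exploratory.

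**The concern.** The detectable difference is the article's only statement of precision, and it treats all 1657 adolescents in the 1 vs 2.2 contrast as independent and equally informative. The article's own design choices contradict this in two ways. Pupils are clustered in 42 schools and will be analysed as such. Exposure and grade also overlap: outside the 2 declining schools every member of group 2.2 was in Primary 7, whereas roughly two thirds of the trial group were in Primary 5 or 6. A grade-adjusted model can use those younger trial pupils only to the extent that unexposed pupils of the same grades exist.

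The Discussion plans to draw inferences from an absence of long-term impact, and 8 points is the only yardstick a reader has for what such an absence could mean.

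**Working it through.** **Inputs.** From the power section: n0 = 456, n1 = 1201, p0 = 0.50, difference 0.08, power 0.80. Alpha is taken as .05 two-sided (z = 1.96). Not in the article, so assumed: ICC 0.01, 0.02 or 0.05; a wait-list arm of about 1201 with the same grade mix as the trial arm; and the share w of wait-list pupils in the 2 declining schools (2/21 if schools are of equal size, range 3% to 20%).

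**1. Reproducing the printed figure.** Let I = n0·n1/(n0+n1) and v = (0.50×0.50 + 0.42×0.58)/2 = 0.2468. Power = Φ(0.08/√(v/I) − 1.96).
- I = 456×1201/1657 = 330.5; SE = √(0.2468/330.5) = 0.0273; power = Φ(0.97) = 0.83.
- Solving for 80% power gives 7.7 points, OR 0.73, which matches the article after rounding.
- The printed alpha of .5 would give 4.2 points (OR 0.85), and one-sided .05 would give 6.8 points (OR 0.76). Neither matches, so .5 is a misprint for .05.

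**2. Clustering alone (42 schools, no grade).** Design effect = 1 + (m − 1)×ICC, with m = 456/21 = 21.7 and 1201/21 = 57.2.
- ICC 0.01: design effects 1.21 and 1.56, effective sizes 378 and 769.
- ICC 0.02: 1.41 and 2.12, effective sizes 322 and 565.
- ICC 0.05: 2.04 and 3.81, effective sizes 224 and 315.

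These give power of about 0.73, 0.63 and 0.45. A generalised least squares calculation with a school random effect and the actual structure of group 2.2 (19 schools with about 18 pupils each, 2 schools with about 57) gives about 0.72, 0.62 and 0.44, with detectable differences of 8.8, 9.8 and 12.2 points. Power at 8 points drops below 0.80 once the ICC exceeds about 0.003.

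**3. Grade, before any clustering.** Group 2.2 is 19% of the sample and the wait-list arm 50%, so 0.38 = w + (1 − w)·g, where g is the Primary 7 share. With w = 2/21, g = (0.38 − 0.095)/0.905 = 0.315.
- The 2 schools hold 1201×2/21 = 114 pupils: about 36 in Primary 7 and 78 in Primary 5-6. The other 19 schools supply 456 − 114 = 342, all Primary 7.
- Primary 7: 378 unexposed vs 378 trial, I = 188.9.
- Primary 5-6: 78 unexposed vs 823 trial, I = 71.6.
- Grade-adjusted I = 260.5, against 330.5 crude (21% less); power = Φ(0.64) = 0.74.
- Without the 2 schools, no grade: 342 vs 1201, I = 266.0; power 0.75.
- Without the 2 schools, with grade: 342 vs 378, all Primary 7, I = 179.4; power 0.58.

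| Share of wait-list pupils in the 2 schools | 42 schools, grade | Without the 2, no grade | Without the 2, grade |
|---|---|---|---|
| 3% (g = 0.36) | 0.70 (9.0 points) | 0.81 (7.9) | 0.65 (9.5) |
| 9.5% (g = 0.315) | 0.74 (8.6) | 0.75 (8.6) | 0.58 (10.3) |
| 20% (g = 0.225) | 0.78 (8.2) | 0.59 (10.3) | 0.42 (12.6) |

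Cells show power at 8 points and, in brackets, the difference detectable with 80% power.

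**4. Both together.** With w = 2/21, the least squares calculation at ICC 0.01, 0.02 and 0.05 gives power of about 0.62, 0.54 and 0.40 for 42 schools with grade, and about 0.51, 0.46 and 0.35 without the 2 schools and with grade.

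**The case against.** - **Exposure is not almost fixed by grade.** A reader might infer that it is, and that the adjusted 1 vs 2.2 contrast is therefore close to uninformative. The definitions do not support this. The trial group spans all grades, and Primary 7 splits about evenly (378 vs 378). Only Primary 5-6 is lopsided, about 91% trial. Grade nearly fixes exposure only inside the wait-list arm. With 42 schools the cost is about 9 points of power. This stands.
- **Grade adjustment is conditional.** The article lists grade as a possible confounder or effect modifier where appropriate, and an unadjusted primary model is also planned. That model reaches 80%, but only if clustering is ignored. This stands, so the grade result is stated as conditional.
- **The repeat need not fall short in every case.** Without grade and without clustering it reaches 0.81 if the 2 schools are small. Detectable differences are also not usually quoted for every repeat. Both stand.
- **70% follow-up is called conservative.** Power of 0.80 at 8 points needs I = 0.2468×(1.96 + 0.84)²/0.0064 ≈ 303. The 42-school grade-adjusted contrast would get there at 70%×303/260.5 ≈ 81% follow-up without clustering. The grade-adjusted repeat would need 70%×303/179.4 ≈ 118%, which is impossible.
- **The models include the baseline school mean of the outcome where available**, which may lower the residual ICC. That is fair, but the residual ICC would have to be about 0.003 or less to keep 80% power.
- **The analysis is exploratory, and data collection is complete.** Results are to be judged on effect size, direction and confidence intervals, and the intervals will show the precision achieved. Nothing in the article says that a null result will be read as excluding 8 points. This limits the consequence but does not make the printed figure right.

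**Conclusion.** The point holds. The 8-point, OR 0.73 figure is correct arithmetic for a crude comparison of independent adolescents at two-sided .05, but it is printed with the wrong alpha and does not describe the planned analyses. Leaving out clustering affects every planned mixed model, and from an assumed ICC of about 0.01 upward it is the larger of the two omissions: power at 8 points is about 0.72, 0.62 and 0.44 at ICC 0.01, 0.02 and 0.05. The overlap of grade and exposure is a further, conditional loss. Before clustering, power is 0.70-0.78 with 42 schools if grade is included, 0.42-0.65 in the grade-adjusted repeat, and 0.59-0.81 in the repeat without grade.

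These sizes rest on assumed ICCs, on the 2 declining schools holding 3% to 20% of wait-list pupils, on equal grade mix in the two arms, and on reading the repeat as applying to 1 vs 2.2 as well as to 1 vs 2. The consequence is an optimistic precision statement in an exploratory study. It is not a failed confirmatory test, and the documents would not support calling it one.

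**What to change.** In Power to Detect a Difference:
1. Correct alpha to .05 and state that it is two-sided.
2. Label 8 points (OR 0.73) as the crude, unclustered figure for 1 vs 2.2.
3. Restate the detectable difference for the mixed model with a stated ICC, for example estimated from the 2012 or 2014 survey data. Give it with and without Wave 1 grade, for all 42 schools and without the 2 nonimplementation schools, using the actual Wave 1 grade-by-group counts in place of the splits assumed here.

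The grade-adjusted figures above should not be copied in as they stand, because those in step 3 of the working carry no clustering allowance.

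The cost is one revised paragraph and a short calculation from data the investigators already hold, with no new participants. The downside is a less favourable stated figure.
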